## Abstract

**Introduction:**

Antipsychotic medication is effective in reducing acute symptoms of psychosis, but it has a range of potentially serious and debilitating adverse effects and is often disliked by patients. It is therefore essential it is only used when benefits outweigh harms. Although multiple trials conducted with people with schizophrenia indicate an increased risk of relapse in the short-term following abrupt antipsychotic discontinuation, there is little evidence about the long-term outcome of a gradual process of reduction and discontinuation on social functioning, relapse and other outcomes.

**Methods and analysis:**

This is a multicentre, randomised controlled trial involving people with schizophrenia and related disorders who have had more than one episode. Participants are randomised to have a clinically-supervised, gradual reduction of antipsychotic medication, leading to discontinuation when possible, or to continue with maintenance treatment. Blinded follow-up assessments are conducted at 6, 12 and 24 months and the primary outcome is social functioning, measured by the Social Functioning Scale at 24 months. A minimum of 134 evaluable participants provides 90% power to detect a five-point difference, and 206 to detect a four-point difference. Secondary outcomes include severe relapse (admission to hospital) and the study is also intended to detect a minimum 10% difference in severe relapse, which requires 402 participants, assuming a 15% loss to follow-up. Other secondary outcomes include all relapses, as identified by an independent and blinded endpoint committee, symptoms measured by the Positive and Negative Syndrome Scale, quality of life, adverse effects, self-rated recovery and neuropsychological measures. Enrolment started in 2016. The trial is scheduled to finish in June 2022.

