## Methods and analysis

### Study design

The trial consists of an open, parallel group randomised trial with concealed, individual randomisation. Randomisation is conducted through an independent, internet-based system linked with the database (https://www.sealedenvelope.com/randomisation/internet/) with 1:1 allocation. There are no replacements for participants who drop out or otherwise cannot comply with study procedures.

Participants and clinicians are aware of allocation, but outcome assessors are maintained blind to intervention arm as far as possible. This is achieved by nominating separate blinded and unblinded researchers at each site, and ensuring that blinded researchers are not exposed to discussions or written information that would reveal allocation. Following follow-up assessment blinded research staff record if they suspect they have guessed arm allocation.

The trial lasts for 2 years, with follow-up assessments conducted at 6, 12 and 24 months post randomisation. The trial design is presented in figure 1. Ethical approval includes the possibility of conducting a longer-term follow-up, and resources will be sought to support this at a later date.

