### Sample size calculation

The primary outcome is social functioning, measured using the Social Functioning Scale.^31^ The literature suggests a minimum difference of between four and five points would be clinically significant, since a difference of four to five points appears to differentiate between patients with good and poor outcomes.^37 51 52^

Using a conventional α of 5% (two-sided) and taking a SD of 8.8 derived from the literature,^53^ a sample size of 134 evaluable participants is required to provide 90% power to identify a five point difference, and a sample of 206 is required to identify a four point difference.

The trial also aimed to establish the safety of the antipsychotic reduction strategy by being powered to detect differences in rates of ‘severe’ relapse (psychiatric hospitalisation), the principal safety measure. We believe that an increased risk of up to 10% would be acceptable to many clinicians and patients if it is balanced by the important outcomes of an improvement in social functioning and reduced side effects. We derived event rates for hospitalisation from those reported in the Leucht *et al*^6^ meta-analysis of antipsychotic discontinuation studies.

We conducted a non-inferiority calculation using a 10% margin of difference. Using a non-inferiority boundary of 10% event rates (severe relapse), with an alpha of 0.05, requires a sample size of 372 for 90% power to exclude a difference of 10% between groups. Adding 15% for attrition brings this up to 402. The lower CI on the absolute scale would exclude a difference of 10% in the situation where non-inferiority was achieved. Four hundred and two participants provides 90% power to detect a difference of 3.1 points on the primary efficacy outcome (the SFS), including an allowance of 15% for attrition or unexpected challenges to the assumptions.

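### The abstract says 402 participants are needed to detect a 10% difference in severe relapse, but 402 comes from a calculation to exclude one; at the event rates that 372 implies, detection power is below 90%

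*Protocol article*

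**What the plan says.** In the Abstract (Methods and analysis), after power statements for the Social Functioning Scale (SFS), the article says that "the study is also intended to detect a minimum 10% difference in severe relapse, which requires 402 participants, assuming a 15% loss to follow-up". It attaches no power to that sentence.

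The Sample size calculation section introduces the same outcome with similar wording: "The trial also aimed to establish the safety of the antipsychotic reduction strategy by being powered to detect differences in rates of" severe relapse, which it calls the principal safety measure. No size of difference is attached to that phrase. It then describes what was done: "We conducted a non-inferiority calculation using a 10% margin of difference", which, "with an alpha of 0.05, requires a sample size of 372 for 90% power to exclude a difference of 10% between groups". Next comes "Adding 15% for attrition brings this up to 402". The event rates are attributed to a published meta-analysis of discontinuation studies, but no rate is printed, and the sidedness of this alpha is not given.

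The last paragraph of that section concedes that a non-inferiority boundary may not be helpful here and that power depends strongly on the event rate. It makes estimation of the rates and their difference, with confidence intervals, the principal aim for severe relapse. It neither withdraws nor corrects the wording about detection.

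**The concern.** A non-inferiority power is conventionally the chance that the confidence interval excludes the margin when the arms truly do not differ. A detection power is the chance of a significant result when the harm is real and equals the stated size. With the same 10 points on both sides, the second generally needs more patients at ordinary event rates, because the variance is larger once one arm has the higher rate. The abstract gives the sample size of the first and describes it as the second.

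Severe relapse is the main safety measure. A reader of the abstract alone would credit the trial with a sensitivity to a 10-point rise in admissions that its sample size was not chosen to provide. The neighbouring SFS sentence, which does state 90% power to detect, makes that reading easy.

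**Working it through.** **Inputs.** From the Sample size calculation section: margin 10 points, alpha 0.05, power 90%, N = 372, attrition 15%, final N = 402. From Study design: allocation "with 1:1 allocation". Assumed because not stated: equal true rates in the non-inferiority calculation; its alpha one-sided at 0.025 or at 0.05; a detection test two-sided at 5%, as the article states for the SFS.

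**1. Reproducing 372.** Per arm, n = (z₁₋α + z₀.₉₀)² × 2p(1−p) / 0.10², with n = 372/2 = 186. Solving for p:

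- One-sided 0.025: (1.960 + 1.282)² = 10.507, so p(1−p) = 186 × 0.01 / (2 × 10.507) = 0.0885 and p ≈ 9.8%.
- One-sided 0.05: (1.645 + 1.282)² = 8.564, so p(1−p) = 186 × 0.01 / (2 × 8.564) = 0.1086 and p ≈ 12.4%.

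So 372 is a plausible non-inferiority figure at a common rate of about 10% to 12%.

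**2. Evaluable number.** The step from 372 to 402 does not reproduce: 372/0.85 = 438 and 372 × 1.15 = 428. That is a separate error, but it leaves the evaluable number unclear. Taking 15% off 402 gives 402 × 0.85 ≈ 342. This also fits the article's SFS claim for 402 participants: 8.8 × √(4/342) × (1.960 + 1.282) = 3.08, against the stated 3.1 points. All three values (342, 372, 402) are carried forward.

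**3. Power to detect a true 10-point increase.** With p₂ = p₁ + 0.10 and p̄ their mean:

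Power = Φ{ [0.10 − z × √(2p̄(1−p̄)/n)] / √([p₁(1−p₁) + p₂(1−p₂)]/n) }

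- 9.8% v 19.8%, n = 171 per arm: (0.10 − 1.960 × 0.03840) / 0.03802 = 0.65; Φ = 74.2%.
- 12.4% v 22.4%, n = 171 per arm: (0.10 − 1.960 × 0.04100) / 0.04064 = 0.48; Φ = 68.6%.

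| Evaluable N | 9.8% v 19.8%, two-sided 5% | 12.4% v 22.4%, two-sided 5% | 12.4% v 22.4%, one-sided 5% |
|---|---|---|---|
| 342 | 74% | 69% | 79% |
| 372 | 78% | 72% | 82% |
| 402 | 81% | 76% | 84% |

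The last column matches the detection test to the one-sided 0.05 from which 12.4% was derived. For 90% power, two-sided at 5%, the totals are 526 evaluable (9.8% v 19.8%) and 600 (12.4% v 22.4%).

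**4. Could one rate make both statements true?** With 342 evaluable, about 90% detection power needs a maintenance rate near 4% (90.2%). With 372, a 5% rate gives 89.8%; with 402, it gives 91.9%. But at a common rate of 5% the non-inferiority formula needs only 164 (one-sided 0.05) or 200 (one-sided 0.025), not 372. No common rate that yields 372 also yields 90% detection power.

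**5. Precision.** Expected 95% confidence-interval half-width at a common 10% rate with 171 per arm: 1.96 × √(2 × 0.10 × 0.90 / 171) = 0.064, or ±6.4 points.

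**The case against.** The best defence is that this is a loose verb. The sample size section names the calculation correctly and prints that the aim is to exclude 10 points. Its phrase "being powered to detect differences in rates of" severe relapse carries no 10-point figure, and the abstract states no power for relapse. All of that is true, and it limits the seriousness. It does not make the abstract correct, because the abstract ties 402 to detecting a 10% difference and nothing later retracts that.

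Second, a reader might infer that the trial risks false reassurance, with a non-significant comparison taken as evidence of safety. The documents do not set that rule. Non-inferiority is judged by whether the confidence interval excludes 10%, and the principal aim is estimation with intervals. If the true excess were 10 points, the non-inferiority test would wrongly exclude it only about 2.5% to 5% of the time. This objection stands against the stronger reading.

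Third, a reader might quote a much lower power by taking a maintenance rate of 20%: 57% with 342 evaluable. The article's own 372 does not support that rate, since the same formula at 20% needs 550 (one-sided 0.05) or 674 (one-sided 0.025).

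Fourth, 342 may be too pessimistic. Outcome measures says that admissions can be obtained from patient records, and Statistical analysis plans a survival analysis, so a missed interview need not lose this outcome. That is fair, and it is why the 402 row is shown. It still falls short of 90%.

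**Conclusion.** The point holds as a misstatement of a design property. The number 402 belongs to a non-inferiority calculation, and the abstract presents it as the number needed to detect a 10-point difference. Under the rates that 372 implies, power to detect a true 10-point increase is 69% to 81% two-sided at 5%, or 79% to 84% one-sided at 5% for the 12.4% rate, depending on how many are evaluable.

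These figures rest on assumptions the article does not confirm: equal true rates, the back-solved 9.8% or 12.4%, and the sidedness of alpha. They concern an increase on reduction, which is the direction the sample size section treats as the risk. The 90% benchmark comes from that section, not from the abstract's relapse sentence.

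Severity is moderate. The outcome is secondary, although it is the principal safety measure; the true basis of the calculation is printed, and estimation is the declared aim.

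**What to change.** In the abstract, replace the clause on detecting a difference with: *to exclude an increase of 10 percentage points in severe relapse (non-inferiority), assuming equal true rates of x%*, with x filled in from the original calculation and the sidedness of alpha stated. In the Sample size calculation section, align the phrase about being powered to detect differences with the non-inferiority calculation that follows it.

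In keeping with the estimation aim, state the expected 95% confidence-interval half-width for the difference: about ±6.4 points at a 10% rate with 342 evaluable. Give any detection power only together with its event rate, evaluable number and alpha.

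The cost is wording only. Design, sample size and analysis do not change, but the property described becomes less favourable than the abstract now suggests.

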**Ethics and dissemination:**

Ethical approval was initially obtained on 27 October 2016 (UK Research Ethics Committee reference 16/LO/1507). Results will be published in peer-reviewed journals and disseminated to the public.

**Trial registration number:**

ISRCTN90298520. EudraCT: 2016-000709-36. Pre-results.

Strengths and limitations of this studyThe trial will be one of the first to provide data on the outcome of a gradual process of antipsychotic reduction and discontinuation in people with schizophrenia and related disorders.The trial will provide relatively long-term outcome data on social functioning as well as relapse and other outcomes.There are likely to be some deviations from the planned treatment strategies.Longer-term follow-up would be desirable and will be initiated in the future.

## Introduction

Schizophrenia and related conditions affect up to 1% of the population,^1^ and are associated with long-term suffering and disability, premature death, physical illness and high costs to individuals and society.^2^ Recommended treatment for people with recurrent episodes consists of continuing antipsychotic medication.^3 4^ Current guidelines do not recommend attempts at reduction or discontinuation of antipsychotics after the first episode, and in practice, antipsychotic treatment is often ‘for life’. In spite of ongoing treatment, many people remain functionally impaired. In one study 25% of people with schizophrenia had severe social disabilities after 15 years, and only 14% had none.^5^

The evidence base for long-term antipsychotic treatment consists of studies showing lower relapse rates with maintenance treatment compared with discontinuation.^6^ However, there are acknowledged methodological problems with these studies.^7^ In addition, several long-term non-randomised cohorts studies find worse outcomes in people who take continuous treatment compared with those who do not, although confounding by indication is likely to be relevant.^8 9^ Criticism of randomised controlled trials includes the fact that most focus on relapse and neglect other outcomes. Follow-up is generally short; only six of 65 studies included in a recent meta-analysis by Leucht *et al*^6^ had followed the participants up for more than a year, and longer duration of follow-up was found to be associated with less difference between maintenance and discontinuation.^6 10^ Moreover, relapse rates may have been inflated by abrupt discontinuation and misidentification of withdrawal-related adverse effects.^11 12^ Some evidence suggests gradual discontinuation may reduce risk of relapse compared with abrupt discontinuation,^13^ although this difference was not confirmed in the analysis by Leucht *et al*.^6^ However, the average taper of 28 days for gradual medication withdrawal may not have prevented discontinuation-related effects in those people who had been taking antipsychotics for many years.

Long-term antipsychotic medication is associated with potentially serious physical complications, including diabetes, tardive dyskinesia and cardiovascular disease.^14–17^ Other adverse effects, such as sexual dysfunction, sedation, emotional blunting and akathisia may be debilitating and unpleasant.^18–20^ Previous research has found that many patients find the adverse effects of antipsychotics burdensome, and would like to try and discontinue the treatment at some stage.^21–23^

There are few long-term follow-ups of people from randomised studies of antipsychotic discontinuation. A 7 year follow-up of an 18 month open trial conducted with people with first episode psychosis found that assignment to a gradual antipsychotic reduction programme was associated with better rates of social recovery and equal rates of relapse compared with maintenance treatment.^24^ Improved levels of neurocognitive performance exhibited by those randomised to antipsychotic reduction at 18 months suggest a possible mechanism for the long-term differences in functional outcome.^25^ In contrast, recent data from a 10 year follow-up of a 1 year, placebo-controlled trial of quetiapine in people with first-episode psychosis reported higher rates of a composite ‘poor outcome’ in people originally randomised to placebo. There were no differences, however, in overall symptom measures, social functioning or quality of life.^26^

Therefore, although continuing antipsychotic treatment has become the norm, it remains unclear whether it has an optimal risk-benefit balance for all people with psychosis or schizophrenia. In particular, more evidence on the effects of gradual reduction of antipsychotics on short and longer-term outcomes could inform practice in this area. Effects on social functioning are particularly important to study because of evidence that long-term antipsychotic treatment may impair social functioning, despite improving symptoms or reducing relapse in the short-term.^24 27^

Further studies are currently being conducted in the first-episode psychosis population.^28^ To date, however, there is no study using gradual and flexible reduction with long-term follow-up in people with more than one episode.

### Aims of trial

The current trial was designed to compare the benefits and harms of a gradual programme of dose reduction and discontinuation of antipsychotic treatment, under clinician guidance, with maintenance treatment in people with a diagnosis of schizophrenia or a related disorder. In particular, the study was set up to test whether such a strategy can improve functional outcomes in people with recurrent or chronic psychosis while minimising the risk of worsening symptoms or relapse.

## Methods and analysis

### Study design

The trial consists of an open, parallel group randomised trial with concealed, individual randomisation. Randomisation is conducted through an independent, internet-based system linked with the database (https://www.sealedenvelope.com/randomisation/internet/) with 1:1 allocation. There are no replacements for participants who drop out or otherwise cannot comply with study procedures.

Participants and clinicians are aware of allocation, but outcome assessors are maintained blind to intervention arm as far as possible. This is achieved by nominating separate blinded and unblinded researchers at each site, and ensuring that blinded researchers are not exposed to discussions or written information that would reveal allocation. Following follow-up assessment blinded research staff record if they suspect they have guessed arm allocation.

The trial lasts for 2 years, with follow-up assessments conducted at 6, 12 and 24 months post randomisation. The trial design is presented in figure 1. Ethical approval includes the possibility of conducting a longer-term follow-up, and resources will be sought to support this at a later date.

**Figure 1 F1:**
[figure not shown]
Trial flow chart.

### Interventions

The antipsychotic reduction protocol was developed after consultation with professionals, academics and the trial’s RADAR Lived Experience Advisory Panel (LEAP). Both the antipsychotic reduction and maintenance protocols are administered by treating psychiatrists. For those participants randomised to the antipsychotic medication reduction arm, an individualised reduction schedule is devised by the research team for each participant based on clinical judgement and adjusted according to the participant’s initial antipsychotic regimen. The dose is reduced incrementally every 1 or 2 months, focusing on one drug at a time where participants are taking more than one antipsychotic. The rate of reduction varies according to baseline dose, with most schedules aiming for discontinuation within 12 months, but some lasting longer where baseline doses are high. Treating psychiatrists are asked to see the participants who have been randomised to antipsychotic reduction approximately every 2 months for the duration of the reduction, to adjust the medication regimen and monitor mental state. The participants are offered the option to discontinue antipsychotic medication completely if the reduction progresses well, or to reduce to a very low dose, defined as the equivalent of 2 mg of haloperidol a day or less, which is lower than the minimum recommended therapeutic dose for most antipsychotics. This is twice the dose that was defined as a ‘low dose’ in the Dutch first episode study,^24^ since some research suggests that doses of antipsychotic medication in people with first episodes should be around half those recommended for people with more established disorders.^29 30^ Guidance on the antipsychotic reduction strategy stresses the need for flexibility, and includes a suggested protocol for the treatment of adverse reactions to withdrawal or symptom exacerbation. Participants randomised to maintenance treatment are requested not to make major reductions in their dose of antipsychotic medication during the trial period. Increases in dose are permitted within the protocol, as are changes to a different antipsychotic agent at the same equivalent dose and minor dose reductions to address side effects.

Participants are monitored by their care team according to usual practice. Patient records are scrutinised by members of the research team every 2 months to monitor the progress of the antipsychotic reduction and adherence to the maintenance protocol. Any deviations, such as participants allocated to reduction not starting or halting their reduction, are discussed with the treating clinician. All changes in antipsychotic doses and use of other medications is recorded throughout the study.

Other drug treatment and interventions such as psychological therapies may be used as indicated throughout the trial.

### Inclusion and exclusion criteria

The eligibility criteria are detailed in box 1. They are designed to make the trial as generalisable as possible to routine clinical practice, while minimising the risks of antipsychotic reduction in those with a history of posing a serious risk to self or others.

Box 1Eligibility criteriaInclusion criteriaAged 18 years or older.A clinical and/or International
Classification of Diseases, 10^th^ Revision, diagnosis of schizophrenia, schizoaffective disorder, delusional disorder or other non-affective psychosis.More than one previous episode or psychotic exacerbation, or a single episode lasting more than 1 year.Prescribed continuing antipsychotic medication.Exclusion criteriaLack of capacity to consent to the trial.Insufficient command of spoken English to understand trial procedures.Subject to a section of the Mental Health Act that includes a requirement to take antipsychotic medication.Clinician considers there will be a serious risk of harm to self or others.Admitted to hospital or treated by a Home Treatment or Crisis Team within the last month.Women who have a confirmed pregnancy.Women who are breastfeeding.Involvement in another Investigational Medicinal Product (IMP) trial.

